### Safety

To ensure patient’s rights, wellbeing and safety, compliance as well as quality of data, an independent and qualified monitor will visit the sites on a regular basis. Frequency of the visits depends on the actual patient inclusion rate and the observed events and deviations.

### Statistical analysis

#### Sample size

From a previous meta-analysis, we know that the median progression-free survival in patients treated with MDRT is 21 months [6]. This corresponds to an event rate of 50% in the MDRT group at 21 months. For the MDRT + ADT group we assume a decreased event rate to 35% (65% event-free). Assuming a constant hazard of 0.0330 in the MDRT group and 0.0205 in the MDRT + ADT group, the metastases progression-free survival at 2.5 years is expected to be 37.1% in the MDRT group and 54.0% in the MDRT + ADT group. This is associated with a hazard ratio of 0.621. Assuming an alpha of 5%, power of 80%, and a dropout of 18% at 30 months, we need to recruit 140 patients per treatment arm and 280 patients in total.

#### Primary endpoint analysis

For the primary endpoint analysis, observations will be censored at 30 months. The MPFS of the two arms will be compared using a Cox proportional hazards regression model to obtain a hazard ratio and accompanying 95% confidence interval. The stratification variables will be accounted for by including these as covariates in the Cox regression [21]. Furthermore, the proportional hazard assumption will be assessed.

For subgroup analysis, an interaction analysis will be conducted to test treatment effect modification with respect to several defined factors, such as number of metastases, type of metastases and location of lymph node metastases. These subgroup analyses should be considered for hypothesis generating rather than hypothesis testing since the trial is not designed to detect these heterogeneous treatment effects.

#### Secondary endpoints analyses

Continuous outcomes will be compared using linear or quantile regression as appropriate. Categorical outcomes will be compared using logistic regression, and time-to-event endpoints will be compared using Cox regression analyses. All analyses will be performed with multivariable adjustment for stratification variables.

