### Evaluation and follow-up

At baseline the investigations include the collection of patient characteristics, a full medical history including PCa characteristics, and the results of the PSMA PET/CT imaging. Baseline toxicity (physician and patient reported) and QoL (patient reported) are recorded. Baseline laboratory assessments include PSA, Testosterone, Haemoglobin (Hb), and Alkaline phosphatase (ALP). The assessments at follow-up include changes in medical history and medication, WHO-performance score, and regular laboratory assessments. Toxicity and QoL will be regularly monitored, and adverse events are reported. The investigations required at baseline and during follow-up are summarized in Table 2.

**Table 2 Tab2:** Follow up after radiotherapy treatment

Required investigation	Baseline	Treatment period		Follow-up				
			1 m after RT	3 m after RT	6 m after RT	9 m after RT	12 m after RT	Every 6 (up to 36 months) months until progression^b^
Eligibility check	X							
Informed consent	X							
ADT (arm 2)		X						
Patient characteristics/ medical history	X		X	X	X	X	X	X
Laboratory assessment								
PSA	X		X	X	X		X	X
Testosterone	X		X		X		X	X
Hb	X			X	X		X	X
ALP	X			X	X		X	X
Whole body PSMA PET/CT^a^	X						X	Every 12 months
Treatment and dosimetric data		X						
Toxicity & QoL								
CTCAE v4	X	X^c^	X	X	X		X	X
RTOG-EORTC toxicity	X	X^c^	X	X	X		X	X
EORTC-QlQ-25	X				X	X	X	X
EORTC-QLQ-C-30	X				X		X	X
SAE		X	X	X	X	X	X	X^d^

^a^ PSMA before inclusion, at progression and for patients without progression only at 12 and 24 months

^b^ 36 months visit, only lab, EORTC-QLQ-C-30 and CTCAE toxicity criteria

^c^ only in case of WPRT or prostate bed RT, the toxicity measurements should be intended at 4th week of treatment course

^d^ Until 2.5 years after treatment completion

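### The covariates stated for the secondary analyses omit the recorded baseline QoL score and toxicity grade: an avoidable, minor loss of efficiency

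*Protocol article*

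**What the plan says.** Under Secondary endpoints analyses, the article assigns linear or quantile regression to continuous outcomes, logistic regression to categorical outcomes and Cox regression to time-to-event outcomes. It then gives one covariate rule for all of them: "All analyses will be performed with multivariable adjustment for stratification variables". Study design lists the stratification variables: number of metastases, metastatic organ (nodal or bone) and presence of local recurrence. None of these is a patient-reported score or a toxicity grade.

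Under Evaluation and follow-up the article says "Baseline toxicity (physician and patient reported) and QoL (patient reported) are recorded". Table 2 confirms this, with a baseline entry for each QoL questionnaire and for both toxicity instruments. The statistical section does not mention these baseline values.

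**The concern.** For a repeated questionnaire, the patient's own baseline score is usually the best single predictor of the later score. The three stratification factors describe the extent and site of disease, and nothing in the article suggests that they could stand in for it. In the first 100 patients two of them were also very unevenly spread (local recurrence in 5, more than 2 metastases in 14), which limits how much variation they can explain.

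QoL matters in this trial. The Background stresses the harm that long-term ADT does to QoL, and the Discussion counts better QoL among the gains expected from a positive result. How much QoL six months of ADT costs is part of judging its value. A model without the baseline score estimates that difference less precisely than the collected data allow.

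**Working it through.** **1. The plan's own figure (Sample size section).** The inputs are "Assuming a constant hazard of 0.0330 in the MDRT group and 0.0205 in the MDRT + ADT group", a hazard ratio of 0.621, and "Assuming an alpha of 5%, power of 80%, and a dropout of 18% at 30 months". Sidedness is not stated; I take two-sided.
- Events (Schoenfeld): 4 × (1.960 + 0.842)² / (ln 0.621)² = 139 after rounding up.
- Dropout hazard: −ln(0.82)/30 = 0.0066 per month.
- Probability of an observed event by 30 months, h/(h + d) × [1 − exp(−30(h + d))]: 0.579 for MDRT and 0.421 for MDRT + ADT, mean 0.500.
- N = 139/0.500 = 278, against 280 stated.

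The stated size reproduces without assuming any gain from covariates.

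**2. QoL models with the baseline score added.** In linear regression the residual variance is multiplied by about 1 − r², and the standard error by √(1 − r²). Strictly, r is the correlation that remains after the stratification factors. It is an assumption. Take a comparison with 80% power without the baseline score. Its expected z-value is 1.960 + 0.842 = 2.802, and the new power is Φ(2.802/√(1 − r²) − 1.960).

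| Assumed r | Variance factor | SE factor | Power (from 80%) | Adjusted n per arm matching 140 unadjusted |
|---|---|---|---|---|
| 0.3 | 0.91 | 0.954 | 83.6% | 127 |
| 0.5 | 0.75 | 0.866 | 89.9% | 105 |
| 0.7 | 0.51 | 0.714 | 97.5% | 71 |

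The factors do not depend on how many patients return questionnaires. With 140 per arm, the difference detectable with 80% power is 2.802 × √(2/140) = 0.335 SD without the baseline score. With 115 per arm (140 × 0.82, rounded) it is 0.369 SD. At r = 0.5 the latter becomes 0.369 × 0.866 = 0.320 SD.

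**3. If the outcome were change from baseline.** With equal variances at both times, a change score has variance 2(1 − r) relative to the follow-up score: 1.40, 1.00 and 0.60 for the three r values. Each exceeds the 0.91, 0.75 and 0.51 above, so adding the baseline score still helps.

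**4. Toxicity models.** The factor 1 − r² does not carry over to logistic regression. The gain depends on the spread of baseline grades, which the article does not give, so I put no number on it.

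**5. Check of the primary Cox model.** I simulated 2,500 trials per setting, with 140 per arm and exponential dropout, calibrated to the MPFS that the plan gives as "expected to be 37.1% in the MDRT group and 54.0% in the MDRT + ADT group". The model was fitted with and without a standardised baseline covariate.

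| Assumed HR per SD of covariate | Power without | Power with |
|---|---|---|
| 1.0 | 79.0% | 79.0% |
| 1.2 | 79.6% | 80.6% |
| 1.35 | 79.6% | 81.5% |
| 1.5 | 79.5% | 83.6% |
| 2.0 | 81.9% | 91.3% |

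The standard error of the log hazard ratio was 0.172 without the covariate and 0.172 to 0.173 with it. Monte Carlo error is about √(0.8 × 0.2/2500) = 0.8 percentage points.

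**The case against.** The strongest objection is that the article never calls the stratification variables the only covariates. It is a condensed text, the full protocol and analysis plan are not shown, and covariate lists for individual scales usually belong there. It also leaves open whether the continuous outcome is the follow-up score or the change from baseline. This lowers the weight of the point but does not remove it. The article does not stay silent on adjustment: it names a set for all secondary analyses, and that set lacks the baseline value. A change score would not close the gap either (step 3).

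It is also fair that r is assumed, and that the exact variance factor holds for linear but not for quantile regression. The direction of the gain in linear regression holds for any non-zero r; its size is uncertain.

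A reader might infer that chance baseline imbalance biases the QoL comparison, the more so because the trial is open. The documents do not support that. Under randomisation such imbalance is already reflected in the standard error, and lack of blinding has no bearing on scores recorded before randomisation.

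**Conclusion.** The point holds as a minor one about the efficiency of secondary endpoints. On the text as written, leaving out the baseline score gives away about 9%, 25% or 49% of the residual variance in a linear QoL model for an assumed r of 0.3, 0.5 or 0.7. Estimates stay unbiased in expectation, type I error is unaffected and the planned primary power is intact.

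A reader might extend the point to the primary model, where "The stratification variables will be accounted for by including these as covariates in the Cox regression", and conclude that it loses precision by leaving out baseline PSA and PSA-doubling time. That does not follow:
- A prognostic covariate in a Cox model does not shrink the standard error of the log hazard ratio (step 5). It moves the target to a more conditional hazard ratio, which may raise power.
- The article gives no prognostic strength for PSA, entry is restricted to PSA below 10 ng/ml, and doubling time is not listed among the baseline investigations.
- The plan's 0.621 comes from arm-level hazards. Treating it as a conditional ratio implies a weaker arm-level effect than planned, so any shortfall in power computed that way is not one in this design.

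Adjusting the primary model for the stratification factors is prespecified, valid and matches the randomisation. More covariates there would be a preference, not a correction.

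**What to change.** Add one sentence to Secondary endpoints analyses, for example: *Each model for a continuous QoL score (QLQ-C30, PR25) also includes the baseline value of the same scale, and each toxicity model includes the baseline grade, beside the stratification variables.* The analysis plan should say how a missing baseline score is handled, so that adjustment does not drop patients. Settle this before outcomes are compared by arm. If the full protocol or analysis plan already says so, no change to the analysis is needed.

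The cost is the sentence itself. The baseline assessments are already in Table 2, and the sample size, visits and primary analysis stay as they are.

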### Inclusion of the first 100 patients

The first patient was included March 2020 and, up to the beginning of December 2021, a total of 100 patients have been randomised at eight different Dutch treatment centres. Patients were randomised to MDRT (*n* = 49) and MDRT + ADT (*n* = 51) and were grouped to number of metastases (≤ 2 *n* = 86 |> 2 *n* = 14), bone or nodal metastases (bone *n* = 28 | nodal *n* = 72) and presence of local recurrence (present *n* = 5).

## Discussion

Current guidelines recommend long term (mostly life-long) ADT for all metastatic patients, including those with oligometastatic disease [1]. Long term ADT, however, does not provide cure, and has a detrimental effect on QoL [6]. Metastasis-directed radiotherapy can effectively ablate metastases in oligometastatic disease. However, progression is observed in > 60% of patients within 2 years after MDRT [13].

We hypothesize that the addition of short-term ADT to MDRT could eliminate undetected metastases and enhance local control of irradiated metastases. Moreover, we aim to improve and standardize patient selection using the most sensitive imaging modality at this moment (PSMA PET/CT).

Positive results of this phase III randomised controlled trial will result in longer PCa disease control, improvement in QoL, sparing of expensive second and third line treatments and potential reduction in cancer mortality.

## Data Availability

Data sharing is not applicable to this article as no datasets were generated or analysed during the current study.

## Abbreviations

PCa: Prostate cancer
BCR: Biochemical recurrence
ADT: Androgen-deprivation therapy
PSMA: Prostate specific membrane antigen
MDRT: Metastasis-directed radiotherapy
MPFS: Metastases progression-free survival
QoL: Quality of life
Hb: Haemoglobin
ALP: Alkaline phosphatase
SBRT: Stereotactic body radiotherapy
WPRT: Whole pelvic fractionated radiotherapy
CTV: Clinical target volume
PTV: Planning target volume
OAR: Organs at risk
LN: Lymph node
GTV: Gross tumour volume
IMRT: Intensity modulated radiotherapy
bPFS: Biochemical Progression-Free Survival
CTCAE: Common Terminology Criteria for Adverse Events
